### Baseline assessment

After consent has been given, baseline data will be collected according to the schedule in table 1.

**Table 1 T1:** Measurements and time points for trial outcomes

	Baseline(preop)	Monthly(postop)	After patient has RTW(postop)	3 months(postop)	6 months(postop)	9 months(postop)	12 months(postop)
Primary outcome (time to full, sustained RTW)		X					
Any RTW		X					
Workplace adaptations and modifications			X				
Demographics	X						
Oxford hip/knee score	X			X	X	X	X
Lower extremity functional scale	X			X	X	X	X
PROMIS social participation	X			X	X	X	X
EQ-5D-5L	X			X	X	X	X
Work Productivity Questionnaire	X			X	X	X	X
Health resource use	X			X	X	X	X
Patient-reported adverse events		X	X	X	X	X	X
Participant adherence and satisfaction (intervention group only)			X				

EQ-5D-5LEuroqol 5 Dimensions 5 LevelsPROMISPatient-Reported Outcomes Measurement Information SystemRTWreturn to work

### Randomisation

Following consent and baseline procedures an authorised, delegated team member at the recruiting site will access REDCap, to obtain the participant’s randomised treatment allocation. An independent statistician at York Trials Unit (YTU), who is not involved in the recruitment of participants, will generate the allocation sequence (to ensure allocation concealment). Allocation will be on a 1:1 ratio (intervention:control) and stratified by surgical site (hip or knee joint) with randomly permuted blocks of randomly varying size.

### Trial treatments

All patients recruited to the OPAL trial receive their usual clinical care as per their local sites standard hip and knee replacement pathway. All patients receive their hospital’s standard preoperative and postoperative assessments and postoperative rehabilitation. In addition to usual care, half of the participants will be randomised to receive the OPAL programme (trial intervention) as described below.

### The OPAL intervention

The aim of the OPAL intervention is to support a safe and sustained RTW after hip and knee replacement. The OPAL intervention contains two complementary elements that provide all the core components of a ‘successful’ occupational intervention for the target population, as demonstrated in the feasibility study.^3^ The two elements are:

Provision of multimedia information resources that support key aspects of RTW.Patient workbook, which aids patients to develop their RTW plan.Employer workbook, which informs employers how to support employees in their RTW.Rehabilitation workbook, which helps patients tailor their exercise programme based on their work and offers a way for patients to track their exercises.OPAL website multimedia resources and rehabilitation videos.RTWC who provides 1:1 support and encourages engagement with and understanding of the provided information resources.

The intervention is designed to accommodate the heterogeneity of paid and unpaid occupations. All the intervention components are required to enable the delivery of a sustainable occupational intervention for this diverse population across a variety of NHS settings that deliver orthopaedic services. Participants only complete the elements of the programme that are relevant/appropriate for them.

The RTWC role facilitates the delivery of the OPAL programme. The RTWCs support the provision of education and support, provide vocational counselling and guidance, signpost to relevant resources and support multidisciplinary team involvement in the RTW process. The 1:1 nature of the interaction between the patient and the coordinator allows for individualised support and helps to ensure RTW is managed sensitively and sympathetically without placing undue pressure on patients to return. The RTWC role aligns with previous research that demonstrates the provision of a coordinator role is positively associated with time to RTW and the probability of return across a variety of healthcare settings.^19 20 22 23^

The role will be adopted by a member of the hospital orthopaedic team, such as nurses, occupational therapists and physiotherapists who will be trained in delivering the intervention. A local hospital orthopaedic team member is best placed to adopt this role due to their knowledge of local treatment pathways, rehabilitation services and the specific needs of their local patient population.

As part of the intervention, the RTWC will contact all patients prior to surgery to review and support their engagement with the information resources and provide vocational advice to aid the development of the RTW plan. They will encourage patients to share the employer booklet and their plan for returning to work with their employer. They remain a point of contact for advice and support post-surgery up to the point the patient returns to work.

Current care is extremely varied in its timing, content, format and mode of delivery^2^ and this presents challenges for the implementation and adoption of a new intervention. The OPAL intervention has been specifically designed to enable implementation across the NHS by allowing flexible delivery within the overarching framework of the intervention’s patient and staff performance objectives to maintain integrity. Delivery of the intervention will be initiated prior to surgery and continue until the patient has either returned to work or until 12 months after surgery (end-of-trial follow-up).

### Control arm

Participants in the control group will be signposted to generic RTW advice and support available via the Royal College of Surgeons of England.^25^

### Data collection

A summary of all data collection is presented in table 1. Data will be collected at baseline (pre-surgery) and 3, 6, 9 and 12 months after randomisation for the patient-report outcome measures (PROMs). Baseline data will include a collection of the individual’s work pattern pre-surgery. The RTW data will be collected monthly until participants have had a fully sustained RTW as defined in the primary outcome. Participants will receive a £10 gift voucher on completing the final trial questionnaire.

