### Trial design

The OPAL trial is a two-arm multicentre, randomised, superiority trial with parallel groups. There will be a 6-month internal pilot and embedded economic and process evaluations. The trial will assess the effect on time to full, sustained RTW of the OPAL occupational support intervention versus usual care in 742 people undergoing elective primary hip and knee replacement in the UK. Participants will be followed-up at 3, 6, 9 and 12 months post-surgery. The participant flowchart can be seen in figure 1. Recruitment is planned to start in April 2023 and finish in July 2024.

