### Outcomes

#### Primary outcome

The primary outcome of the OPAL trial is time until ‘full’ sustained return to any work, defined as work resumption to the same hours as prior to joint replacement, in any role, without any day of sick leave for a consecutive 4-week period.

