### Follow-up and withdrawal

Participants will be followed-up at 3, 6, 9 and 12 months, as well as monthly for a maximum of 12 months or until the primary outcome is achieved. Participants will be sent a maximum of two reminders via their preferred method of contact to complete their questionnaires, with a final attempt to obtain data by telephone.

Participants can withdraw from the trial at any point during the trial by directly contacting the trial team at YTU, or their clinical team. If a participant indicates that they wish to withdraw from the trial, they will be asked whether they wish to withdraw from the intervention only (ie, withdrawal from engaging with the RTWC and workbooks) or withdraw fully from the trial. Where withdrawal is only from the intervention then follow-up data will continue to be collected. Participants will be informed that they do not have to give a reason for their decision to withdraw from the trial. However, if the participant indicates the reason this will be recorded. Data provided by participants who withdraw will be retained for analysis up until the point of withdrawal—as detailed in the patient consent.

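### The Data collection section times the patient-reported outcomes from randomisation, while every other place that names an origin for these visits uses surgery

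*Protocol article*

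**What the plan says.** The Data collection section of the protocol article sets the schedule for the patient-reported outcomes: "Data will be collected at baseline (pre-surgery) and 3, 6, 9 and 12 months after randomisation". Two statements elsewhere use a different origin, and so does the table that the section itself relies on:

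- Trial design: "Participants will be followed-up at 3, 6, 9 and 12 months post-surgery".
- Table 1, under Baseline assessment: the first follow-up column for these measures is headed "3 months(postop", and the 6, 9 and 12-month columns carry the same postoperative label. Data collection points to this table immediately before the sentence in question: "A summary of all data collection is presented in table 1".
- The OPAL intervention: delivery continues until return to work or "until 12 months after surgery (end-of-trial follow-up".

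The remaining places that mention these visits or the 12-month period name no origin: the Abstract, Follow-up and withdrawal, Intervention fidelity and qualitative outcomes, and Economic evaluation.

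**The concern.** Surgery and randomisation are different dates. Participants are identified from surgical waiting lists and are randomised after consent and a preoperative baseline, and the coordinator then contacts the intervention group before the operation. The gap between the dates is whatever wait remains, and the article sets no limit on it.

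The Oxford scores, LEFS and PROMIS are there to describe functional recovery, and the article says that group differences will be reported at all available time points. A time point has a clear meaning only if it marks the same stage of recovery in everyone. QALYs are built from EQ-5D-5L at baseline and each follow-up over 12 months, so they depend on the same visits. A score missed at the intended recovery stage cannot be collected later.

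**Working it through.** **Figures in the plan.** No figure in the article depends on this anchor. The sample size of 742 is derived for time to return to work and does not use the timing of the patient-reported outcomes. The check is therefore a comparison of text plus a simple shift of dates.

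**Step 1: order of events.** Recruitment and informed consent, Baseline assessment and Randomisation together give this order: waiting list, consent, preoperative baseline, randomisation, surgery. Let w be the months from randomisation to surgery, so w is positive. The documents give no value; 1, 3 and 6 months are assumed for illustration.

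**Step 2: where each visit falls.** On the surgery clock, a visit labelled m months falls at m months of recovery for everyone. On the randomisation clock it falls at m − w months after surgery:

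| Assumed wait w | 3-month visit | 6-month visit | 9-month visit | 12-month visit |
|---|---|---|---|---|
| 1 | 2 | 5 | 8 | 11 |
| 3 | 0 | 3 | 6 | 9 |
| 6 | −3 | 0 | 3 | 6 |

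A negative value is a preoperative measurement. Any wait over 3 months makes the visit labelled 3 months preoperative.

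**Step 3: spread within one visit.** If waits ran from 1 to 6 months, each nominal visit would cover 6 − 1 = 5 months of recovery, which is wider than the 3-month spacing between visits.

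**Step 4: QALY horizon.** On the randomisation clock, 12 months comprise w months before surgery and 12 − w after: 1 and 11, 3 and 9, or 6 and 6 for the three assumed waits. On the surgery clock the recovery stage is fixed, but the preoperative baseline EQ-5D-5L then lies about w months before the origin (taking baseline as close to randomisation). Baseline to last visit spans about 12 + w months: 13, 15 or 18. Neither clock removes the variation, so the QALY origin needs its own statement.

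**The case against.** The strongest reply is that this is a slip of one word. The sentence directly follows a reference to Table 1, whose columns are postoperative, and Trial design and the intervention section agree with the table. A trial team would probably schedule from surgery, in which case no harm arises. That is a fair reading, and it makes the harm conditional on the randomisation clock being the one applied. It does not remove the error. The article fixes the anchor in two incompatible ways, and Follow-up and withdrawal, where a reader would look to settle the matter, names none. The wait may also be short, since screening can take place at the preoperative assessment; a small w shrinks the shift in proportion.

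A reader might go further and infer three things that the documents do not support.

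- **That the primary analysis loses events or power.** The sentence is limited to the patient-reported outcomes. Return to work has its own sentence and its own monthly postoperative column in Table 1, and sick days are counted from surgery. Follow-up and withdrawal gives a limit without an origin ("as well as monthly for a maximum of 12 months or until the primary outcome is achieved"), but the intervention section places the end of follow-up 12 months after surgery. No text starts the return-to-work clock at randomisation.
- **That one arm is favoured.** The clock would apply to both arms alike, and nothing in the article shows that waits differ by arm.
- **That the formal time zero for "time until ‘full’ sustained return to any work", or the handling of participants never operated on, is a defect here.** Such detail is commonly left to the statistical analysis plan or full protocol, which are not shown.

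**Conclusion.** The Data collection sentence is wrong as written. It contradicts Trial design, Table 1 and the intervention section, which are all the other places that name an origin for this follow-up. If it were followed, each patient-reported visit would move earlier in recovery by the participant's wait: by 1, 3 or 6 months under the assumed values, with the 3-month visit on the day of surgery at 3 months and preoperative beyond that. The consequence would be added noise and blurred time-point contrasts in the functional scores and EQ-5D-5L, and a QALY horizon with a varying preoperative share.

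This rests on two conditions: that the randomisation clock is the one implemented, and that waits are long or variable enough to matter. The documents settle neither. Because the effect is confined to secondary and economic results and the intended schedule can be recovered from three other places, this is a correction to make but not one on which the validity of the trial turns.

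**What to change.** In Data collection, replace the reference to randomisation with surgery, so that the sentence matches Trial design, Table 1 and the intervention section. Confirm that the REDCap trigger for the 3, 6, 9 and 12-month questionnaires is the recorded date of surgery. State the QALY time origin in the promised health economic analysis plan, including how the interval between the preoperative baseline EQ-5D-5L and surgery is treated; the choice of origin is a trade-off for the health economists.

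The cost is a wording change, one system check and a short statement in a plan still to be written. No new data, no added analysis and no change to the sample size are needed.

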### Outcomes

#### Primary outcome

The primary outcome of the OPAL trial is time until ‘full’ sustained return to any work, defined as work resumption to the same hours as prior to joint replacement, in any role, without any day of sick leave for a consecutive 4-week period.

#### Secondary outcomes

- Time to any RTW.

- Measures of functional recovery to daily activities and social participation:

Oxford Hip/Knee Score (OKS/OHS)^26 27^—joint-specific, PROMs designed to assess disability in patients undergoing hip (OHS) or knee (OKS) replacement. Each score contains 12 questions scored on a 5-point scale (0–4 points) producing scores ranging from 0 (poor function) to 48 (good function).Lower Extremity Functional Scale (LEFS)^28^—a valid self-reported patient-rated outcome for the measurement of general lower extremity function. It contains 20 questions each scored on a 5-point scale (0–4 points) producing scores ranging from 0 (very low function) to 80 (very high function). It has been shown to have good measurement properties compared with the SF36 and WOMAC scores^29^—WOMAC (Western Ontario and McMaster University Osteoarthritis Index) is disease specific for hip or knees and is scored by the patient. SF36 (Short Form 36 Health Survey Questionnaire) is used to indicate the health status of participant populations.PROMIS social participation short form questionnaires (eg, ability to participate questionnaire, satisfaction with social roles and activities questionnaire, satisfaction with participation in social roles questionnaire)^30 31^—PROMIS (Patient-Reported Outcomes Measurement Information System) is a set of person-centred measures that evaluates and monitors physical, mental and social health. We will use the social health tools developed by PROMIS to measure social participation and satisfaction with participation and social roles.

- Number of ‘sick days’ between surgery and ‘full’ sustained RTW.

- Participant adherence to the intervention and the intervention’s physical rehabilitation programme (including self-reported, 5-point Likert scales (very helpful, helpful, neither helpful nor unhelpful, unhelpful, very unhelpful)).

- Proportion of participants using workplace interventions, adaptations and modifications to facilitate their RTW (eg, changes in working hours and shift patterns, changes to work role or work environment or use of additional equipment within the workplace).

- Health-related quality of life (Euroqol 5 Dimensions 5 Levels (EQ-5D-5L)).^32^

- Work productivity (Work Limitations Questionnaire).^33 34^

### Data storage

REDCap will be used to capture all trial data electronically. To minimise attrition, we will use multiple methods to keep in touch with participants.

Data will be held securely on the cloud-hosted REDCap server. Access to the trial interface will be restricted to named authorised individuals granted user rights by a REDCap administrator at YTU. All trial files will be stored in accordance with Good Clinical Practice (GCP) guidelines. Trial documents (paper and electronic) held at YTU will be retained in a secure location for the duration of the trial. All work will be conducted using the University of York’s data protection policy which is publicly available.

### Follow-up and withdrawal

Participants will be followed-up at 3, 6, 9 and 12 months, as well as monthly for a maximum of 12 months or until the primary outcome is achieved. Participants will be sent a maximum of two reminders via their preferred method of contact to complete their questionnaires, with a final attempt to obtain data by telephone.

Participants can withdraw from the trial at any point during the trial by directly contacting the trial team at YTU, or their clinical team. If a participant indicates that they wish to withdraw from the trial, they will be asked whether they wish to withdraw from the intervention only (ie, withdrawal from engaging with the RTWC and workbooks) or withdraw fully from the trial. Where withdrawal is only from the intervention then follow-up data will continue to be collected. Participants will be informed that they do not have to give a reason for their decision to withdraw from the trial. However, if the participant indicates the reason this will be recorded. Data provided by participants who withdraw will be retained for analysis up until the point of withdrawal—as detailed in the patient consent.

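### The withdrawal rule gives controls no option that keeps follow-up, and neither arm a level that keeps return-to-work status without questionnaires

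*Protocol article*

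**What the plan says.** The Follow-up and withdrawal section of the Protocol article sets the rule. A participant who indicates a wish to leave the trial is asked "whether they wish to withdraw from the intervention only (ie, withdrawal from engaging with the RTWC and workbooks) or withdraw fully from the trial". The consequences are stated for each choice: "Where withdrawal is only from the intervention then follow-up data will continue to be collected"; otherwise, "Data provided by participants who withdraw will be retained for analysis up until the point of withdrawal".

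The section on the OPAL intervention describes the RTWC and the workbooks as components of the trial intervention. For the comparator, the Control arm section says: "Participants in the control group will be signposted to generic RTW advice and support available via the Royal College of Surgeons of England".

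The primary outcome is collected by monthly self-report (Table 1). On its duration, the Data collection section says: "The RTW data will be collected monthly until participants have had a fully sustained RTW as defined in the primary outcome". The Follow-up and withdrawal section gives the same limit: "monthly for a maximum of 12 months or until the primary outcome is achieved".

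Unreturned forms are dealt with separately from withdrawal: "Participants will be sent a maximum of two reminders via their preferred method of contact to complete their questionnaires". If these bring no reply, the trial team makes one last try by phone.

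**The concern.** The only option that preserves data after a request to withdraw is defined by things that one arm does not receive. An OPAL participant who wants to stop can leave the programme and still be followed up. A control participant making the same request can only leave completely. In neither arm can someone who has had enough of the questionnaires, and says so by asking to withdraw, agree to be asked now and then whether they are back at work.

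This bears on the primary analysis because the article names no source for time to full sustained RTW other than the participant's own monthly reports. Full withdrawal before the event ends observation, and the person is censored in the Cox model. The monthly forms continue only for people who have not reached sustained RTW, so slower returners meet more of them and have more occasions to withdraw. If those who leave would have returned later than those who stay, the censoring is informative. If this happens at different rates in the two arms, the hazard ratio is biased.

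**Working it through.** **1. Options by arm.** Setting the withdrawal rule beside the descriptions of the two arms gives:

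| What the participant wants | OPAL | Control |
|---|---|---|
| Leave the RTWC and workbooks, stay in follow-up | Available | Nothing to leave |
| Stop questionnaires, still give RTW status | Not described | Not described |
| Leave the trial fully | Available | Available |
| Leave some forms unanswered, without asking to withdraw | Reminders, then telephone | Reminders, then telephone |

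The asymmetry is in the first row and the gap common to both arms is in the second.

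**2. Who is affected.** Only full withdrawals before the event matter for the primary outcome. Someone who has already had sustained RTW keeps their event. Under an exponential model with the sample-size section's median of 3.2 months, the control proportion with an event by 12 months is 1 − 2^(−12/3.2) = 1 − 2^(−3.75) ≈ 0.93. Most participants would therefore have an event within follow-up if they stayed in. Being event-free when censored does not by itself make censoring informative, since that is true of everyone censored. Bias needs withdrawal to be related to the later chance of returning, beyond what the model's covariates explain.

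**3. The plan's own allowance.** The sample-size section allows 20% attrition. The stated total of 742 can be reproduced closely:
- Events for a hazard ratio of 1.34, 90% power and two-sided 5% (sidedness assumed): 491.
- Probability of an event over 12 months, at the mean of the two medians, 3.2 and 3.2/1.34 months: about 0.949. So 491/0.949 ≈ 517 participants.
- Design effect 1 + (31 − 1) × 0.01 = 1.30 in the RTWC arm only, averaging 1.15 over both arms; then 517 × 1.15/0.80 ≈ 743, against 742 stated.

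The allowance covers 0.20 × 742 ≈ 148 participants. It protects power and does nothing about censoring that differs by arm.

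**4. Illustration of possible bias.** The article gives no withdrawal rates, so every input here is assumed except the median of 3.2 months, the hazard ratio of 1.34 and the 12-month limit. Assume that 30% of participants are slow returners with 0.3 times the hazard of the rest, that the effect within each class is 1.34 or 1.00, and that withdrawal occurs at 0.5 to 4 months among slow returners only. The table gives the fitted Cox hazard ratio from two simulation runs of 60,000 participants per scenario.

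| Withdrawn before return, control v OPAL | Effect present (runs 1; 2) | No effect (runs 1; 2) |
|---|---|---|
| None | 1.283; 1.27 | 1.004; 1.00 |
| About 8% in each | 1.260; 1.28 | 1.009; 1.00 |
| About 8% v 4% | 1.222; 1.24 | 0.961; 0.97 |
| About 12–13% v 4% | 1.194; 1.19 | 0.937; 0.93 |

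Simulation noise: the standard error of the log hazard ratio is at least 2/√60,000 ≈ 0.008, or about ±0.02 on a hazard ratio of 1.28. The first two rows are therefore indistinguishable. At 8% v 4% the ratio to the no-withdrawal value runs from 1.222/1.283 = 0.95 to 1.24/1.27 = 0.98, a fall of about 2 to 5%. At 12–13% v 4% it is 1.194/1.283 = 0.93 to 1.19/1.27 = 0.94, a fall of about 6 to 7%.

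**5. How strong these inputs are.** If all withdrawers come from the 30% slow class, 8.3% of controls is 8.3/30 ≈ 28% of slow controls and 12.7% is 12.7/30 ≈ 42%. In OPAL, 3.8% is 3.8/30 ≈ 13%. If the OPAL arm withdrew more instead, the bias would reverse: with no effect, exchanging the arms turns 0.961 into 1/0.961 ≈ 1.04.

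**The case against.** The strongest reply is that the rule applies only to people who ask to withdraw. A reader might infer that anyone wanting fewer questionnaires is lost to the primary outcome. The article does not support that: missing forms are met with reminders and a telephone attempt, and nothing treats non-return as withdrawal. Nor is a withdrawer's information discarded, since data up to that point are kept and an event already recorded still counts.

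A reader might also infer that controls will withdraw more, biasing the result against OPAL. That does not follow. The intervention-only option answers a motive that exists only in OPAL, namely tiring of the programme. For questionnaire fatigue both arms face the same options, and OPAL carries extra contact. Direction and size are unknown, and the illustration shows material bias only when an arm difference is put in by assumption.

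The endpoint is also more than one date: it needs pre-surgery hours and four consecutive weeks without sick leave. A single question at month 12 would measure it less well than monthly reports. That stands, and it shapes the fix.

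Finally, this is a condensed article, and a fuller protocol may describe more withdrawal levels. But the article does not leave the matter elsewhere. It states the choice put to the participant, and its data-access section presents the paper as a full account of the protocol while also mentioning a separate one. If that document has a third level, the two need only be aligned.

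**Conclusion.** The point holds as a weakness in a stated rule. For those who ask to withdraw, the only option that keeps follow-up is confined to the OPAL arm, and no reduced-contact level is described for either. Primary-outcome data that some withdrawers might willingly give are therefore not sought under the rule as written.

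The consequence is a possibility. Censoring at full withdrawal could be informative and could differ by arm; the article has no figures from which to judge whether it will. The hazard-ratio shifts of 2 to 7% rest on assumed unequal rates confined to slow returners and are not a forecast. The sample size of 742 is unaffected. The change is worth making because it is cheap and protects the primary outcome.

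**What to change.** In Follow-up and withdrawal:
- Add a third level, offered in the same words in both arms. It stops the PROM and monthly questionnaires but allows brief text or telephone contact for RTW status and date, asked against the definition in the Primary outcome section. Contact should preferably be at short intervals to limit recall, and the last no later than month 12.
- At any withdrawal, with the participant's agreement, ask one closing question on RTW status and date: returned to full hours, returned in part, not returned, or no longer intending to return.
- Reserve full withdrawal for those who decline all further contact.

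Dates obtained this way rest on longer recall than monthly reports. Flag them, and add a sensitivity analysis that censors these participants at the time they left the questionnaires.

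The cost is a revised withdrawal form, a line in the participant information (a minor amendment), a few texts or calls per person at this level, and one more status to track in REDCap. The right to leave completely is unchanged.
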